## Abstract

**Introduction:**

Environmental hygiene and food safety are important determinants of child stunting. This research aims to explore the relationship between child stunting and household hygiene practices and behaviours, including the availability of water, sanitation and hygiene (WASH) facilities; the use of safe food and good quality drinking water (especially when used for complementary feeding); hygienic practices in food transport, storage and preparation and the control of cross-contamination from animals, their produce and waste.

**Methods and analysis:**

This study is part of a wider observational study which aims to investigate the interdisciplinary factors contributing to child stunting using a ‘whole child’ paradigm. The observational study recruits women during pregnancy in Hyderabad, India, Lombok, Indonesia and Kaffrine, Senegal, and dyads (ie, 500 mother–infant pairs per country) are followed longitudinally up to 24 months after birth. Within the interdisciplinary niche, the study here has developed tools to investigate the potential exposure pathways to environmental pathogen contamination of foods and water. Holistic WASH and food safety data collection tools have been developed to explore exposure pathways at the household level, including: (1) survey questionnaires; (2) spot-checks; (3) biological sampling of drinking water, food and domestic surfaces and (4) direct observation. An integrated analytical approach will be used to triangulate the evidence in order to examine the relationships between child stunting, WASH and food safety behaviours.

**Ethics and dissemination:**

Ethical approval of the study was granted by the ethics committee of the LSHTM, RVC, ILRI, ICMR, IIPHG, SEAMEO-RECFON, University of Cheikh Anta Diop. Findings of the study will be disseminated through publication in peer-reviewed journals, relevant international conferences, public engagement events, and policy-maker and stakeholder events.

WHAT IS ALREADY KNOWN ON THIS TOPICFrom the moment complementary feeding begins, the chances of exposure to food contamination and infectious disease increase exponentially.Adequate water, sanitation and hygiene (WASH) and food safety practices can play a key role in reducing infectious disease transmission and child malnutrition.The contribution of hygiene behaviours and food contamination in driving transmission of infections and childhood stunting requires further investigation.WHAT THIS STUDY ADDSDevelopment, application and analysis of integrated WASH and food safety tools, towards a holistic understanding of how these practices and behaviours impact child stunting.Evidence towards a new typology of child stunting, with a focus on exposure pathways for pathogens, and to support programmes and policies to minimise stunting in childhood.HOW THIS STUDY MIGHT AFFECT RESEARCH, PRACTICE OR POLICYUnderstanding of the role of home hygiene and food safety related practices in childhood stunting with a view to identify solutions.New and more integrated approaches in research and practice that bring together WASH and food safety considerations at the household level to investigate exposure to pathogens.Evidence on complementarities between food hygiene and WASH in order to help design suitable interventions to combat stunting.

## Introduction

The incidence and severity of stunting in childhood is closely linked to exposure to infection from food, drinking water and the wider environment.^1^ Infections associated with contaminated water or insufficient water, sanitation and hygiene (WASH) are responsible for an estimated 21% of the total global burden of diseases,^2^ contributing to the outbreak and chronicity of preventable infections such as diarrhoeal diseases and acute respiratory infections, which are the two leading causes of death in children globally.^3^ However, three recent randomised controlled trials have assessed the impacts of WASH combination interventions on nutrition in Bangladesh,^4^ Kenya^5^ and Zimbabwe.^6^ The studies were not able to detect any effects on child linear growth, and only in Bangladesh was diarrhoea reduced.^7^ Cumming *et al* have challenged the efficacy of the WASH interventions in addressing common causes of faeco-oral disease in low-income contexts, such as cryptosporidium.^8^ More generally, the interventions did not increase the quantity of water supply available to practice domestic hygiene.

In addition, the WHO Foodborne Disease Burden Epidemiology Reference Group (FERG), estimated that approximately 40% of the global burden of foodborne diseases occurs in children under the age of 5 years.^9^ A common cause of foodborne infections is the consumption of raw or undercooked meat, fish, seafood, eggs, fresh produce and dairy products contaminated by norovirus, Campylobacter, non-typhoidal Salmonella or pathogenic *Escherichia coli.*
9 Food hygiene is a primary concern in the preparation of complementary foods—for example, bottles often cannot be adequately sterilised and perishable complementary foods are often left unrefrigerated or eaten using unclean utensils or with unwashed hands.

Disease transmission from faeces can be foodborne or waterborne (ie, oral ingestion of contaminated food and water), water washed or water scarce (ie, spread through inadequate hand and food hygiene) and water based (ie, transmitted by parasites that penetrate skin in water, such as schistosomiasis or by walking barefoot on contaminated soil in the case of hookworm).^10^ For example, theory and evidence suggests that pathogens in foods are a main driver of infant faecal-oral disease.^11^ Field studies have demonstrated high bacterial contamination from *E. coli* or Salmonella in weaning foods.^12 13^ Of particular importance for the cleanliness of infant complementary foods are the quality of water, surfaces and utensils used to prepare and eat them^14–16^ as well as the quality of the food ingredients procured.

Hence, the availability of WASH and food storage and preparation facilities is likely to determine exposure to infection. Nonetheless, pathogen exposure can also arise when available facilities are used inadequately. For example, cultural norms and beliefs can restrict domestic food and hygiene practices—for example, whether mothers are the principal decision-makers about food preparation and hygiene in the household, or whether women are able to use the same toilet facilities as other household members.^17^ However, while contamination of foods during cooking and feeding is common, the behavioural drivers have not been adequately explored. A recent systematic survey of 350 WASH evaluation projects in low-income and middle-income countries found that around 15% of studies examined nutrition outcomes like stunting, and handwashing before food preparation, but only 5% reported on other food hygiene behaviours, such as whether food was stored appropriately and kitchen utensils were washed.^18^

While food safety and WASH are interlinked, to date little attention has been paid to understanding the relationships and trade-offs between food safety, WASH and child stunting. The safety of livestock and fish derived foods is a particularly neglected area and there has been no systematic integration of these topics in food safety and WASH protocols.^14^ The UKRI GCRF Action Against Stunting Hub (AASH) explores child stunting from the Whole Child Approach, that is, considering different aspects of child development, including biology considerations, the home environment, the educational environment and the food system, that can contribute to thriving childhood. The aim of this study is to examine WASH and food safety elements, their convergence and contributions to child stunting at the household level. It evaluates WASH and food safety practices across households in three study sites with the objective to provide evidence on potential exposure to pathogens through contaminated environment, drinking water, and complementary food, and associated risk factors.

## Methods and analysis

### Conceptual framework

The manner in which WASH and food safety at the household level can potentially lead to changes in infection and dietary intake, thereby affecting child stunting, is illustrated in figure 1, adapted from the UNICEF’s (1990) conceptual framework on the causes of malnutrition.^19^ Inadequate WASH practices and food safety can contribute to childhood stunting directly, by exposing infants to infection via complementary foods contaminated during preparation and storage, or through feeding with unclean utensils, including the hands of carers. The safety of foods can also be compromised before arrival at households, throughout the different steps and processes of the food value chain. Those food hazards can be intrinsic to the food produced (eg, pathogens from animal diseases, heavy metal marine contamination), or extrinsic through processing and handling (eg, inadequate hygienic practices, aflatoxin contamination during storage).^20^ Mechanisms include nutrient loss (eg, during diarrhoeal episodes), energy used by the immune system (eg, in combating illnesses), and increased intestinal permeability and reduction in nutrients absorption (eg, enteropathy).^21^

**Figure 1 F1:**
[figure not shown]
A conceptual framework showing the linkages of WASH and food safety with stunting at the household level. WASH, water, sanitation and hygiene.

In theory, access to adequate WASH facilities enables appropriate drinking water, hygiene and food safety practices, contributing to reduction in transmission of foodborne and waterborne pathogens and improving nutrient uptake, and ultimately child growth and development.^20^ Drinking water may be contaminated at the point of supply, or through transport and storage.^15 16^ The availability of clean water is critical for optimal hygiene practices,^10^ to address contamination by human and animal faeces,^22^ and to prepare food hygienically. Sanitation facilities can enable safe faeces disposal, especially those of young children, which can be particularly pathogenic.^23^ Faecal contamination can also come from the presence of domestic and wild animals or pests inside the household or in surrounding spaces.^24^ It is expected that these sources of infection become more important as a child starts crawling and interacting with their environment. As such, understanding of the determinants of food and hygiene practises in the household is key to improving infant health and nutrition.^25^

Along with direct exposure, there is also an indirect route from water supply and sanitation facilities to childhood malnutrition, which operates through the opportunity costs of resource use. The time carers have to observe, correct, and address unhygienic behaviour, and the scarcity of time in relation to competing activities that need to be done by carers in the home or workplace, may also be detrimental for children’s nutritional outcomes.^26^ For example, it is typically women and older children, both of whom are more likely than others to be carers of young children, who spend time fetching water, engaging with animal fodder and collecting firewood. This may occur at the expense of adequate childcare and feeding, food preparation, education or rest.^27^ When drinking water needs cannot be met affordably, households may need to purchase less food in order to afford enough water to drink. This kind of trade-off is clearly more prevalent for the poorest households, for whom malnutrition is also likely to be highest.

The WASH and food safety approaches, including their scope, evolution and methods are described in table 1. Combining both WASH and food safety approaches provides an opportunity for more effective integration and learning of the two disciplines and their contributions to child growth and development. The two should converge when looking at household units with a central focus such as child stunting.

**Table 1 T1:** Characteristics of water, sanitation and hygiene (WASH) and food safety and veterinary public health research

	WASH	Food safety and veterinary public health
Scope	To investigate deficiencies in water supply and quality, sanitation and hygiene to improve public health. Also, to evaluate the adequacy of hygiene standard to minimise foodborne diseases risks, and the role of water supply and sanitation access as enabling factors for improving child care, health and nutrition.	To pursue a comprehensive ‘farm to fork’, ‘stable to table’, ‘boat to throat’ approach to prevent and minimise risks of food contamination at all stages of the food chain from production to human consumption and waste management.
Sector	Human-centred with a strong anchor in the public health sector.	Focus on animal source foods, zoonoses and their respective risks.
Evolution	Historically, WASH research has focused on water-related disease transmission from human excreta (faecal-oral diseases). This has contributed to understanding the mechanisms of faecal-oral infection through waterborne, water-washed and water-based routes. Early intervention studies focused on the provision of infrastructure, and information, education and communication. Current research focuses more on behaviour change communication using bottom-up approaches, and incorporating the ‘A (Animals)’ into WASH more holistically.^24^	Veterinary public health traditionally looked at all food chain stages to identify where risks (eg, biological, chemical and physical) can emerge and how to prevent or mitigate them. The initial focus was on microbiological aspects with a strong technical dimension. Veterinary public health now looks at human behaviour more widely, bringing in social science aspects and economics to understand better practices and the motivations behind them. There is a (slow) move towards systems thinking, and a lot of progress in quantitative microbiological and epidemiological studies, detection techniques, etc.
Research methods	Interventions (eg, randomised controlled trials). Cross-sectional, questionnaire- based surveys. Longitudinal questionnaire-based surveys. Spot checks. Direct observation. Biological sampling and testing. Risk assessments. Qualitative research on behaviour, practices and perceptions, including participatory approaches.	

### Study design

This is a multicountry longitudinal observational study where women are recruited during pregnancy in Senegal, Indonesia and India and mother–infant pairs are followed up to 24 months after birth. Average stunting prevalences in these three countries selected are medium (17.9% in Senegal) to very high (30.8% in Indonesia and 37.4% in India).^28^ This protocol involves multiple approaches to assess WASH and food safety practices in urban or rural households of women enrolled in the study, in Hyderabad city, India, East Lombok, Indonesia and Kaffrine, Senegal, at predefined time points (see AASH observational cohort description in Heffernan *et al* in this supplement, including further details on the study setting, sampling process, participant schedule, data collection and quality control, data management, etc).

### Data collection

This WASH and food safety data collection protocol focuses on three areas: exposure pathways to wider environmental pathogens, foodborne hazards and waterborne hazards. Four data collection tools for the household-level have been developed, namely: (1) a module for WASH and food safety to be included to the cohort questionnaire-based interviews (see online supplemental appendix 1); (2) spot-checks (see online supplemental appendix 2); (3) biological sampling and (4) direct observation (see online supplemental appendix 3). The interviews and spot-checks take place simultaneously during home visits at 9, 12 and 18 months after birth. Data will be collected throughout the different seasons. Direct observation and biological sampling are conducted during a separate subsequent visit at each time point, in a subsample of the cohort. No additional inclusion or exclusion criteria were considered in the selection. Food and water samples are kept to a minimum for the analysis required, namely half filling a 50 mL Falcon tube with food served to the child, and the measure of the container in which the child is normally given drinking water, respectively.

10.1136/bmjpo-2022-001695.supp1Supplementary data

The food safety component of the data collection focuses on nutrient-rich foods with the potential to alleviate stunting, particularly on animal source foods (ASFs). This is due to their important nutritional profile,^29^ their documented potential to alleviate stunting^30–33^ and their high food safety risk profile. Selected ASFs will be considered at each country, according to their relevance.

Trained enumerators collect data using electronic tablets in all study households, as summarised in table 2. The direct observation tool is recorded on paper and enumerator positioning and previous rapport creation are used as ways to minimise bias. Privacy is maintained by stopping the direct observation on the respondent’s request. Data collection tools developed in English are translated into local languages and backtranslated into English to check for accuracy, and piloted in the field.

**Table 2 T2:** Summary of the integrated study methods and tools used to assess WASH and food safety at the household level

Tool	Description	Sample size
Questionnaire-based interview	Mothers are asked about infant and young child feeding practices, household food expenditure and the main household decision-makers and influencers of these activities. Physical activity questionnaires ask mothers about the times spent on work and housekeeping including collecting water, fodder and fuel. Furthermore, there are questions on water sources, water security, sanitation and handwashing. Other questions focus on the practices of acquisition, transport, storage, preparation of ASF and the points of potential contamination in the household. Finally, other questions refer to the presence and behaviour of animals and potential transmission pathways associated with close proximity to animals, such as direct contact between animals and children or food. The hazards and risks prior to arrival of ASFs in the household are elucidated in a separate component, at the value chain level (see Cooper *et al* in this supplement).	Whole cohort (500 households per country)
Spot-check	Enumerators observe behavioural issues alongside the interview questionnaire. The data are recorded using a check list on the availability and type of sanitation facilities available at the households (eg, the place for defecation and proximity), handwashing infrastructure (eg, location, availability of water and soap), presence of animals (eg, livestock, pests), food storage facilities and practices (eg, functioning refrigerator) and food preparation (eg, easy to clean equipment).	Whole cohort (500 households per country)
Direct observation	Enumerators stay at the household for 3 hours around a feeding event, observing the mothers perform their daily activities and taking a passive approach to blend into the background in order to better observe hygiene related behaviours. Structured observation include activities related to water collection and storage, as well as personal, environmental and food hygiene (food preparation, storage, child feeding, handwashing and animal contact). This data collection method is a gold standard for actual observation of behavioural practices.	Subsample (approximately one-third of full cohort in each country)
Biological sampling and testing	Enumerators collect samples of stored water, foods to be consumed by the children (as close to the feeding of the child as possible) and a swab of the main food preparation area at the households. Samples of hands rinse are optional. The samples are stored in a coolbox and transported to a specialised laboratory for analysis. The samples are processed in-country and tested for overall contamination and for selected pathogens (such as Salmonella, Shigella, *Escherichia coli* and Campylobacter for food and *E. coli*/faecal indicators for surfaces and water), using standard laboratory protocols (of conventional culture and PCR). Part of the samples collected are used for lab analysis and the remaining part stored under −20°C for future analysis and crosschecking.	Subsample (approximately one-third of full cohort in each country)

ASF, animal source foods; WASH, water, sanitation and hygiene.

### Data management and analysis

Data are collected at the households in CommCare and checked for accuracy before being transmitted to a central repository and can be downloaded in Excel for analysis. Samples are analysed at laboratories in each of the countries using tailored standard operating procedures.

Descriptive, comparative and regression analyses will be used to investigate the impact of WASH and food safety on child stunting. Factors relating to WASH and food safety amenities and practices will be considered simultaneously as external risks or preventive factors influencing the incidence and severity of stunting, using multivariable statistical approaches. To relate the main exposure variables (WASH and food safety factors) with the main outcome (stunting, measured as either z-scores or presence/absence), multivariable regressions models will be developed. According to our causal framework presented in figure 1, we will adjust this model for potential confounding factors. Some of these confounding factors will be fairly stable (eg, sex, maternal literacy, household facilities, socioeconomic status) and others will be time-varying (eg, age, breastfeeding, environmental hygiene levels). We will avoid intermediate factors (eg, infection rates). Subsequently, we will explore the potential role of the mediators in the causal framework using mediation analysis. Due to the existence of repeated measures conducted over three different time points for each child, we will account for this with a random effect term by individual in the regression model. The model will be a linear regression for stunting measured as a continuous variable, and a logistic (or ordered logistic) regression for stunting (moderate and severe) measured as a dichotomous variable. Due to the fact that in our three country settings the relevant association might differ, we will estimate the models separately in each country, and afterwards we will conduct individual participant data meta-analysis of the coefficients of interest across the countries. This strategy will allow for an optimal fit of the model in each country and at the same time we will be able to explore the heterogeneity of coefficients across countries and within subgroups (by age, sex and socioeconomic characteristics).

Data triangulation will also be used, first, to address biases in individual data collection tools. For example, known biases occur when measures are reported by participants, particularly by those people for whom illness becomes normalised after repeated bouts of infection.^34^ Observation of behaviours, through enumerator presence in the household at certain times of day, can help to mitigate reporting bias. However, surveys and observation may also affect participant motivation, particularly when repeated over long periods. Extensive collection of samples for laboratory testing can be done, but have their own weaknesses.^35^ Second, data triangulation through statistical modelling will be used to determine the relationship between WASH and food safety in each of the study contexts, and to explore relevant questions such as whether they are complements or substitutes in child health and nutrition. As such, a mix of approaches is being used in this study to address these potential challenges.

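### Environmental hygiene, and apparently household facilities, are listed as confounders although the article also treats them as exposures; adjusting a facility effect for hygiene conditions on an intermediate

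*Protocol article*

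**What the plan says.** Under Data management and analysis, the article sets out "To relate the main exposure variables (WASH and food safety factors) with the main outcome (stunting, measured as either z-scores or presence/absence") by multivariable regression. The exposures cover both infrastructure and behaviour and are taken together: "Factors relating to WASH and food safety amenities and practices will be considered simultaneously as external risks or preventive factors".

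The adjustment variables are to follow the causal framework in figure 1 and are given as examples. The first group is "Some of these confounding factors will be fairly stable (eg, sex, maternal literacy, household facilities, socioeconomic status"). The second group, followed directly by the rule on mediators, reads "others will be time-varying (eg, age, breastfeeding, environmental hygiene levels). We will avoid intermediate factors (eg, infection rates"). A mediation analysis is planned as a later step.

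Elsewhere the same items are exposures. The Abstract opens with environmental hygiene as a determinant of stunting and includes availability of WASH facilities in the research question. In Table 2, the spot-check records sanitation and handwashing infrastructure, and direct observation records environmental hygiene.

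The Conceptual framework section gives the causal order: "access to adequate WASH facilities enables appropriate drinking water, hygiene and food safety practices, contributing to reduction in transmission of foodborne and waterborne pathogens", and from there to growth.

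**The concern.** Environmental hygiene is both something whose effect is to be estimated and something to be adjusted for. On the natural reading the same is true of household facilities. This does no harm where the variable precedes the exposure in question. It does harm where the variable follows from the exposure, because part of the effect is then held constant.

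The clear case is a facility exposure, such as the type of toilet, the water source or a handwashing station. If facilities work partly by making the home cleaner, a coefficient adjusted for cleanliness shows only what remains by other routes. A small coefficient could then be read as little benefit from facilities when it only means little benefit beyond hygiene. The Introduction already cites three randomised trials that detected no effect of WASH interventions on linear growth, so such a misreading would be easy to make. The country-specific coefficients are to be combined in a meta-analysis, which would carry the same meaning into the pooled result.

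**Working it through.** The article gives no effect estimate, power or mediated share for this model, so there is no figure to reproduce. The check is a comparison of the text, followed by an illustration.

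**1. Role of each item**

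| Item | As exposure | As confounder | Position in the article's framework |
|---|---|---|---|
| WASH facilities | Abstract; Table 2 (spot-check); analysis section (amenities) | Analysis section, if household facilities includes them | Upstream: they enable practices |
| Environmental hygiene | Abstract; Table 2 (direct observation) | Analysis section, time-varying list | Plausibly downstream of facilities |
| Breastfeeding | Not stated | Analysis section, time-varying list | Not placed downstream of WASH anywhere |

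The second row conflicts with the rule against intermediates when the exposure is a facility. The first row conflicts only if household facilities means WASH facilities, which the article does not define.

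**2. What the adjustment removes**

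Let F be facilities, H environmental hygiene and Y the height z-score, with socioeconomic status (SES) a measured common cause of all three.

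- H = a·F + SES term + noise
- Y = d·F + b·H + SES term + noise
- Total effect of F: T = d + a·b
- Coefficient of F adjusted for SES only: T
- Coefficient of F adjusted for SES and H: d
- Share lost: (T − d)/T = a·b/T = m, the mediated share

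Assumed values, none from the documents: T = 0.20 per unit of F and a = 0.5. Then b = 0.20·m/0.5 = 0.4·m, and d = 0.20·(1 − m). At m = 0.5, b = 0.20 and d = 0.10, and d + a·b = 0.10 + 0.5 × 0.20 = 0.20.

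A simulation with 400,000 records, fitted by ordinary least squares, gave:

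| Mediated share m | F adjusted for SES | F adjusted for SES and H | Expected d |
|---|---|---|---|
| 0% | 0.199 | 0.199 | 0.20 |
| 25% | 0.200 | 0.149 | 0.15 |
| 50% | 0.201 | 0.102 | 0.10 |
| 75% | 0.201 | 0.050 | 0.05 |
| 100% | 0.203 | 0.001 | 0.00 |

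The loss equals the assumed share by construction. The simulation confirms the algebra and says nothing about the true share.

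**3. The reverse case: hygiene as the exposure**

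At m = 0.25, b = 0.10 and d = 0.15. Given SES, F has variance 1 and H has variance 0.5² × 1 + 1 = 1.25, so the slope of F on H is 0.5/1.25 = 0.4. Leaving facilities out gives b + d × 0.4 = 0.10 + 0.06 = 0.16 (simulated 0.162). Including them gives 0.10 (simulated 0.103), the true value. Adjusting for facilities is therefore correct here.

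No single set serves both exposures. If F and H enter one model, the coefficient of F is a direct effect, while that of H is its effect given facilities.

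**The case against.** The strongest reply is that this is a condensed article. Both confounder lists are examples, more than one model is foreseen, and the stated basis is figure 1, which could not be read here. Nor does the article say that each coefficient is a total effect. Entering WASH and food safety factors together serves a stated aim, namely whether they complement or substitute for one another. This has force against any claim that a single fixed model is certain to be used. It does not remove the conflict: the prose of the Conceptual framework section gives the causal order without the figure, and the examples are the ones an analyst would follow.

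Four stronger readings are tempting, and the documents do not support them.

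- **Breastfeeding is a mediator.** The nearest text is the carer-time route, of which the article says "This may occur at the expense of adequate childcare and feeding, food preparation, education or rest". That concerns feeding in general. Breastfeeding plausibly affects both intake of complementary food and water and growth, so it is an ordinary confounder unless the framework says otherwise.
- **Household facilities is the exposure itself.** The term is undefined, stands beside literacy and socioeconomic status, and may include non-WASH amenities. For practice exposures it belongs in the model.
- **Hygiene cannot be both confounder and mediator.** Causal roles depend on the exposure. Hygiene can mediate a facility effect and confound a food-practice effect. The framework also traces faecal contamination to animals and pests, so hygiene is not merely a product of facilities or practices.
- **The model adjusts away the WASH effect.** There are many exposures, and only the mediated part of a facility effect is lost.

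**Conclusion.** The point holds for facility exposures. Following the stated adjustment list would condition the effect of WASH facilities on environmental hygiene, which the article's own framework places after them, and this contradicts its rule on intermediates. The conflict over household facilities depends on a definition that the article does not give; the conflict over hygiene stands either way.

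The size is the mediated share, anywhere from 0 to 100%. A reader might infer a loss of at least half, or that the study is bound to report a null effect of WASH. Neither follows, because no share is given.

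The exact equality of loss and mediated share assumes a linear model without interaction, hygiene measured without error, and no unmeasured common cause of hygiene and growth. It does not carry over exactly to the logistic models. The direction of the concern does not depend on the illustrative 0.20. The matter should be settled before analysis, because it decides what the main coefficients mean.

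**What to change.** Specify the adjustment set separately for each exposure tier, derived from the figure 1 framework:

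1. **WASH facilities, total effect.** Adjust for socioeconomic status, maternal literacy, child age and sex, and other variables that precede the exposure. Leave out environmental hygiene and practices, and take hygiene up as a mediator in the planned mediation analysis.
2. **Practices, hygiene and measured contamination.** Keep facilities as a confounder. Keep environmental hygiene wherever it is not downstream of the exposure under study.
3. **Breastfeeding.** Keep it as a confounder unless the framework places it downstream of the exposure in question.

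State whether household facilities means WASH facilities, other amenities or both. Interpret each coefficient only from the model built for that exposure. A simultaneous model can be kept for the question of complements and substitutes, with its coefficients labelled as mutually adjusted (direct) effects.

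The cost is wording in the analysis plan and a few additional model runs. No new data are needed.
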